#### Dyspnea evaluation

Second, an additional form containing the modified Medical Research Council Dyspnea Scale (mMRC) will be inserted into patients’ medical records on paper. It is a validated patient symptom questionnaire for a subjective assessment of COPD symptoms. This intervention will address the recommendation of National Institute for Health and Care Excellence based on Fletcher et al. [31].

GPs will be asked to determine the patient’s status according to the scale and put this information into the patient’s medical records.

#### COPD check list

Third, a checklist for practitioners will be provided with information about what should be done while consulting on a patient with COPD. This intervention will address the recommendation of the European Respiratory Society [32]. It will cover points such as that a patient should be given basic information about COPD, its treatment, and the expected effects of applied drugs, making the patient an active, aware participant in their long-term treatment. GPs will be asked to provide patients with the information and tick a box if it is done.

#### Demonstration inhaler devices

Finally, practices will be provided with training inhaler device sets for health care staff and train GPs on how to instruct patients to use devices properly. This intervention will address the recommendation of the Polish Society of Lung Diseases [33].

GPs will be asked to teach patients in the correct use of each device and record information about the fact in patient’s medical records.

### Control group

In this arm, GPs will provide their usual care for COPD patients. The practices in the control group will receive feedback after the end of the study about their own performance in comparison with the performance of other practices in the study in relation to the guideline recommendations. The GPs will receive no intervention during the study.

### Outcomes/measures

#### Primary outcome

The primary outcome will be the GPs’ adherence to the recommendations, which is dichotomized as follows. A positive score is given if all recommendations are followed, while following less than four recommendations is given a negative score. Data listed in Table 3 will be obtained from the patients’ medical records (independent of the checklist that is provided as part of the intervention) and during interviews. All identified COPD patients who gave informed consent in each practice will be included, and full data protection procedures will be followed.

**Table 3 T3:** Information recorded in patients’ records to determine adherence of a GP the recommendations

1.	Brief anti-smoking counselling performed
2.	Dyspnea assessed
3.	Management process of COPD assessed
4.	Training patient on correct use of inhaling device performed.

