## Abstract

**Background:**

Chronic obstructive pulmonary disease (COPD) remains a major health problem, strongly related to smoking. Despite the publication of practice guidelines on prevention and treatment, not all patients with the disease receive the recommended healthcare, particularly with regard to smoking cessation advice where applicable. We have developed a tailored implementation strategy for enhancing general practitioners’ adherence to the disease management guidelines. The primary aim of the study is to evaluate the effects of this tailored implementation intervention on general practitioners’ adherence to guidelines.

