Preliminary qualitative evidence from the authors’ earlier work showed that not one single guideline for COPD was used by all GPs or medical specialists. However, responders pointed out the individual recommendations most commonly used and the barriers to their implementation. The identified barriers for adhering to specific recommendations were: (1) lack of knowledge on smoking cessation brief intervention, (2) dyspnea evaluation tool was unavailable, (3) lack of a care plan, and (4) lack of demonstration-inhaling devices. Other research has indicated that the treatment parameters from the (COPD) guidelines are not always measured [17-19]. The consequence is that not all patients receive recommended advice and treatment from their physicians.

This study is part of the Tailored Implementation for Chronic Diseases (TICD) international collaborative research project, which is being undertaken in Germany, Norway, Poland, the Netherlands and the United Kingdom. The aim is to develop and test methods of tailoring knowledge-implementation interventions to determinants of practice in chronic illness care [20]. In Poland, the focus is on the implementation of COPD guidelines in primary care. The research group in Poland selected four key recommendations applicable to primary care (Table 1) from the four COPD guidelines most relevant to primary care and used in Poland.

**Table 1 T1:** Key recommendations for COPD management

A	Brief smoking cessation counseling is effective and every tobacco user should be offered stop-smoking advice at every contact with health care providers.
B	The prognosis of COPD should be estimated using the mMRC dyspnea scale.
C	The patient should be given the basic information about his/her disease, its treatment and the expected effects of applied drugs, in order to enhance that the patient takes an active, participating role in the long-term treatment.
D	The patient should be trained in the correct use of all devices which he/she will use for inhalation.

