### Eligibility criteria

#### Patients

Eligible patients will be approached at follow-up. Only patients who were treated in the same practice at baseline (with the labelled medical records) will be considered for inclusion so that the study is prospective. Exclusion criteria are: (1) terminal illness and (2) cognitive impairments. At follow up 80 patients, randomly selected (with personal data unknown to researchers) will receive an informed consent form and an invitational letter via their GPs, and will be asked to fill in a questionnaire and/or participate in an audio taped interview or focus group. This letter will provide comprehensive information about the study. Contact details of the researchers will be provided so that patients can ask questions. Patients’ information gathered from questionnaires or from interviews will be anonymized.

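### Taken literally, the all-four scoring rule counts correct care of non-smokers, and of patients without an inhaler, as non-adherence, which caps and dilutes the primary outcome

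*Protocol article*

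**What the plan says.** The protocol article scores the primary outcome per patient (Primary outcome): "A positive score is given if all recommendations are followed, while following less than four recommendations is given a negative score". Table 3 lists what must be found in the record. Its first item is "Brief anti-smoking counselling performed" and its fourth is "Training patient on correct use of inhaling device performed". There is no category for an item that does not apply.

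The denominator is broad: "All identified COPD patients who gave informed consent in each practice will be included". Patients are identified by ICD-10 code J44. The patient eligibility section says: "Exclusion criteria are: (1) terminal illness and (2) cognitive impairments". Neither smoking status nor inhaler use is a condition of entry.

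The recommendations being scored are narrower. In Table 1 (Background), recommendation A reads: "every tobacco user should be offered stop-smoking advice at every contact with health care providers". Recommendation D reads: "The patient should be trained in the correct use of all devices which he/she will use for inhalation". The Abstract also limits the smoking component: "particularly with regard to smoking cessation advice where applicable".

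The sample size section plans for 40% versus 60% adherence. It attaches those rates to selected COPD recommendations and does not link them to the all-four score.

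**The concern.** A GP who gives no cessation advice to a never-smoker has not departed from recommendation A. Under the rule as written, that patient still has at most three of four items performed and is scored negative. The same holds for item 4 in a patient with no inhaling device. The score therefore departs from the stated objective, which is physicians' adherence to the four recommendations.

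Two consequences follow. Adherence in either arm has a ceiling below 100%, set by the patient mix and not by GP behaviour. If the planning rates describe GP behaviour where the recommendations apply, the observable arm difference shrinks in proportion to that ceiling, and the planned power is not delivered.

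**Working it through.** **1. The plan's own figure.** Inputs from the sample size section: 40% versus 60%, 80% power, two-sided alpha 0.05, ICC 0.05, 30 patients per practice.

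- Two proportions, pooled variance, no continuity correction: [1.960 × √(2 × 0.5 × 0.5) + 0.842 × √(0.24 + 0.24)]² / 0.20² = 96.9, so 97 per arm.
- Design effect: 1 + (30 − 1) × 0.05 = 2.45.
- 97 × 2.45 = 237.65 per arm; 237.65 / 30 = 7.92, so 8 practices per arm, 16 practices and 480 patients.
- Plus 10%: 16 × 1.1 = 17.6, so 18 practices.
- Patients per practice at baseline: 30 / (0.58 × 0.65) = 79.6, so 80.

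All of these reproduce. The arithmetic is sound for an outcome that can reach 100%.

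**2. The ceiling.** Let *a* be the share of patients to whom all four items apply (tobacco users who also use an inhaling device). Under the literal rule, composite rate = *a* × (adherence among those patients), so it cannot exceed *a*. An observed 60% needs adherence of 0.60 / *a* among them: 67% at *a* = 0.9, 75% at 0.8, 86% at 0.7, 100% at 0.6. Below 0.6 it is impossible.

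**3. The value of *a*.** The article does not give it, so it is an assumption, shown here from 0.36 to 1. The low end is only an illustration: it is the national rate in men in the Background (34% daily + 2% occasional = 36%; for women 23% + 3% = 26%). These are general-population figures, not figures for COPD patients.

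**4. Power if 40% versus 60% holds only among patients to whom all four items apply.** This is a further assumption.

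- Effective sample size per arm: 9 × 30 / 2.45 = 110.2.
- Observed rates: p₁ = 0.4*a*, p₂ = 0.6*a*.
- SE = √{[p₁(1 − p₁) + p₂(1 − p₂)] / 110.2}.
- Noncentrality = (p₂ − p₁) / SE, referred to *t* with 18 − 2 = 16 degrees of freedom (critical value 2.12).

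Example at *a* = 0.7: rates 0.28 and 0.42; SE = √[(0.2016 + 0.2436) / 110.2] = 0.0636; noncentrality = 0.14 / 0.0636 = 2.20; power 54%.

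| *a* | Composite rates | Power |
|---|---|---|
| 1 | 40% vs 60% | 81% |
| 0.9 | 36% vs 54% | 73% |
| 0.8 | 32% vs 48% | 64% |
| 0.7 | 28% vs 42% | 54% |
| 0.6 | 24% vs 36% | 45% |
| 0.5 | 20% vs 30% | 37% |
| 0.36 | 14% vs 22% | 26% |

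A normal approximation with pooled variance gives somewhat higher values (85% at *a* = 1, 77% at 0.9, 68% at 0.8, 59% at 0.7, 49% at 0.6, 40% at 0.5) and the same pattern. All figures hold the ICC at 0.05. Any extra between-practice variation from differing smoking shares is not included, because the article gives nothing from which to size it.

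**The case against.** The best reply is that the rule can be read more mildly. Advice addressed to tobacco users is not breached when a non-smoker goes without it. The Abstract limits that component to where it applies, and the implementation programme pairs counselling with identification of smoking status. An assessor might credit a recorded non-smoker, and item-level coding might sit in a fuller document that is not shown. This stands in part: the negative score for non-smokers is the literal reading, not the only one. But the article does more than stay silent. It states a closed rule with items worded as actions performed, and that rule conflicts with the recommendations it scores. Leaving the credit to discretion would also be risky. The Blinding section says outcome assessment is unblinded, and only intervention GPs are trained to identify smoking status, so the arms could be credited differently.

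The size is also open to challenge. The applicable share is unknown. The article calls COPD strongly related to smoking, and the Polish studies it cites report more than 70% of patients on inhaled steroids, so *a* need not be near the low end. If 40% and 60% were meant as composite rates, the planned power is unchanged and only attainability is in doubt. Both points stand, which is why a range is shown.

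A reader might go further and infer that the outcome largely measures smoking prevalence, or that the trial no longer answers its question. The article does not support that. Practices are randomised, so smoking share falls equally on both arms in expectation, and the arm difference still reflects adherence, diluted by *a*. Chance imbalance across 18 practices can add noise, but its amount has not been shown.

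**Conclusion.** The concern holds as a misfit in a stated primary-outcome rule. Applied as written, the rule scores guideline-concordant care of an uncounselled non-smoker as non-adherence and caps the composite at *a*. It is certain that the scored items and the recommendations cover different patients, and that 60% cannot be reached if *a* is below 0.6. The power loss is conditional on the unknown *a* and on 40% and 60% describing adherence among patients to whom all four items apply. On those assumptions, power is already 73% at *a* = 0.9 and 45% at 0.6, against a planned 80%. The main effect is dilution of the arm difference, plus some added between-practice variation of unknown size.

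**What to change.** Before data lock:

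- Define the primary outcome as all recommendations applicable to that patient followed, with a non-applicable item counted as met. Every patient stays in the denominator and the ceiling returns to 100%.
- Set applicability of items 1 and 4 from baseline smoking and inhaler-prescription status, taken the same way in both arms and not from records created by the intervention. Follow-up smoking status should not be used, because change in smoking status is itself an outcome.
- As a sensitivity analysis, report the patients to whom all four items applied at baseline.
- State that the 40% and 60% planning rates refer to this composite, or restate the power for it.

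The cost is modest. Interventions have been delivered, but outcome data are extracted at the end of the study, and the Secondary outcomes section already has records reviewed for smoking status and COPD medication. Some patients will lack a recorded baseline smoking status and will need the planned multiple imputation. A patient whose smoking or inhaler use changes after baseline is scored on baseline status. The sensitivity subset is smaller: with 30*a* patients per practice, 9 practices per arm, ICC 0.05 and 40% versus 60%, the normal approximation gives power of 79% at *a* = 0.7, 72% at 0.5 and 58% at 0.3.

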**Methods/Design:**

A pragmatic two-arm cluster randomized trial has been planned to compare care following the implementation of tailored interventions of four recommendations in COPD patients against usual care. The study will involve 18 general practices (9 in the intervention group and 9 in the control group) in Poland, each with at least 80 identified (at the baseline) patients with diagnosed COPD. The nine control practices will provide usual care without any interventions. Tailored interventions to implement four recommendations will be delivered in the remaining nine practices. At follow-up after nine months, data will be collected for all 18 general practices. The primary outcome measure is physicians’ adherence to all four recommendations: brief anti-smoking advice, dyspnea assessment, care checklist utilization and demonstration to patients of correct inhaler use. This measurement will be based on data extracted from identified patients’ records. Additionally, we will survey and interview patients with chronic obstructive pulmonary disease about the process of care.

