### Sample size calculation

The sample size calculation indicated that, for a two-arm cluster controlled randomized trial, a minimum number of 16 primary care practices with minimum of 30 COPD patients per practice is required. A total of 16 clusters and at least 480 subjects is required at baseline and follow-up (8 clusters in each study arm) to detect a difference, or change in adherence, of between 40% and 60% with selected COPD recommendations, between the intervention group (facilitating adherence to guidelines) and the control group without intervention (usual care), with 80% power, a two-tailed alpha of 0.05, and intra-cluster correlation of 0.05.

A standard sample size formula was used to calculate the initial unadjusted sample size requirements, followed by appropriate adjustment for clustering by general practice according to Campbell *et al.*[23], with expected small clustering effect (ICC = 0.05). Previous reported ICCs vary from 0.03 for smoking advice [23] to 0.05 for cluster randomized trials in primary care (data from Trial of Older People in the Community) [24,25]. It was decided to increase the sample by 10% to account for contingencies such as non-response or recording error, giving a total of 18 practices.

With regard to the number of patients with COPD per practice, an assumed response rate of 58% [26,27] and a dropout of 35% [28], which led to a total of 80 COPD patients needed per general practice at baseline. Patients will be selected via the medical records using ICD code J44, and medical records will be labelled at the baseline of the study.

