### Data collection

At the end of the study data will be collected by review of medical records of COPD patients identified at the baseline who visited their GPs during the last nine months. Extracted information will cover the following: brief anti-smoking advice performed, information about dyspnea, COPD checklist utilization and training on using inhalers.

Patients with COPD who have given signed informed consent will be asked to fill in a questionnaire and participate in an interview containing questions about the process of care, information received from GPs and patients’ health status perception.

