### Statistical methods

The primary analysis will be on an intention to treat basis. Missing values will be inputted with a multiple imputation method. Data will be coded, cleaned and locked before any analyses are made. Quantitative data will be analyzed in aggregate, using the Statistical Package for the Social Sciences (SPSS, (version 17, IBM Corp.) and Statistica (v10, StatSoft Inc.). Study groups will be compared with respect to the determinants of COPD and its improvement. Only members of the research team who need access to the database to fulfill their roles within the study will be granted access to the database. Demographic characteristics of the practices and the participants within the practices will be described using percentages, measures of central tendency (means or medians) and measures of variation (standard deviations or ranges). The analysis will be based on the patients nested within practices two-level model. The primary endpoint is the GPs adherence to four COPD guidelines after nine months, in each practice. Secondary endpoints are the change in smoking status and health care utilization during the nine months amongst included patients. Data will be compared between arms using logistic regression (with logit link function and binomial distribution) with patient at level one and practice at level two. The ICC and odds ratios and 95% confidence intervals will be estimated using two-level random intercepts logistic regression models. The significance level will be set at α = 0.05 for all analyses.

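### The primary analysis set is stated inconsistently, and the consenters-only version is formed after randomization and does not match the intention-to-treat claim

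*Protocol article*

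**What the plan says.** All places are in the protocol article.

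- **Abstract, Methods/Design:** "This measurement will be based on data extracted from identified patients’ records". No consent or visit condition is attached.
- **Primary outcome:** "All identified COPD patients who gave informed consent in each practice will be included". The same section names interviews, besides records, as a source for the Table 3 items.
- **Data collection:** the outcome items come from "review of medical records of COPD patients identified at the baseline who visited their GPs during the last nine months". Signed consent is mentioned only for the questionnaire and interview.
- **Eligibility criteria, Patients:** "Eligible patients will be approached at follow-up". Eighty randomly selected patients "will receive an informed consent form and an invitational letter via their GPs", and the letter concerns a questionnaire, interview or focus group. Record review is not named.
- **Setting and participants; Blinding:** practices are randomized after practice-level consent, records are labelled at baseline, and GPs cannot be blinded.
- **Statistical methods:** "The primary analysis will be on an intention to treat basis", with multiple imputation for missing values. The section does not say which patients are analysed.
- **Sample size calculation:** 80 patients per practice follow from "an assumed response rate of 58" per cent and a 35% dropout.

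**The concern.** The denominator of the primary endpoint can be read in three ways, and the choice could be made after the data are seen.

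The consent-based reading is the most troublesome. Agreement is obtained once the intervention has run, and it passes through the clinicians whose recorded behaviour is being scored. A patient who has just been counselled and shown an inhaler may be readier to sign than one who has not, and that tendency may differ between arms. If so, the comparison no longer rests on the randomized practices' full cohorts.

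A random intercept for practice does not correct selection that depends on arm. Multiple imputation helps only if non-consenters stay in the set as missing. If they are excluded by definition, it never reaches them.

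**Working it through.** **1. Does the sample size settle which set is meant?** Inputs from the Sample size calculation: 40% vs 60%, two-sided alpha 0.05, power 80%, ICC 0.05, 30 patients per practice.
- The standard two-proportion formula (pooled variance, no continuity correction) gives 97 per arm.
- Design effect: 1 + (30 - 1) x 0.05 = 2.45.
- 97 x 2.45 = 237.65 per arm; 237.65 / 30 = 7.92, so 8 practices per arm, 16 practices and 480 patients. The plan's figure is reproduced.
- 16 x 1.1 = 17.6, so 18 practices. 30 / (0.58 x 0.65) = 79.6, so 80 patients per practice.

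The arithmetic is sound. Applying a response rate suits a consent- or response-based set better than a full record review, but the text does not say so.

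**2. How much of the baseline cohort remains?** 0.58 x 0.65 = 0.377, and 80 x 0.377 = 30.2. About 62% of labelled patients are expected to leave the set after randomization.

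**3. What could selection do?** This is an illustration, and its selection ratios are assumptions that are not in the document. Suppose true adherence is 40% in both arms. In the intervention arm only, adherent patients are r times as likely to be included as the others. Observed adherence there is 0.4r / (0.4r + 0.6). With 9 practices of 30 per arm, the effective n is 270 / 2.45 = 110.2 per arm. The rejection rate is from a noncentral t with 16 df and noncentrality equal to the difference divided by its standard error.

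| r | Observed | Noncentrality | Rejection of a true null |
|---|---|---|---|
| 1.1 | 42.3% | 0.35 | 6% |
| 1.25 | 45.5% | 0.82 | 12% |
| 1.5 | 50.0% | 1.50 | 29% |
| 2 | 57.1% | 2.58 | 68% |

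A normal approximation gives 6%, 13%, 32% and 72%.

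The visit condition can act the other way. If 28 of 100 labelled patients are adherent in each arm, but 70 visit in control and 80 in intervention, the visitors-only rates are 28/70 = 40% and 28/80 = 35%. That would work against the intervention.

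**4. Does a full baseline set gain power?** Same t method, 9 practices per arm, 40% vs 60%:
- 30 per practice: 81%.
- 80 per practice (design effect 1 + 79 x 0.05 = 4.95; effective n 720 / 4.95 = 145.5): 90%, but only if 40% and 60% apply to the whole labelled set.
- If those rates apply to visitors, 70% visit (an assumption) and non-visitors are scored as not followed, the contrast becomes 28% vs 42%. Power is then about 66% with 80 per practice. With 52 per practice (80 x 0.65, reading dropout as leaving the practice, which the document does not say) it is about 62%.
- At 90% visiting the corresponding figures are 84% and 80%.

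**The case against.** Several points on the other side stand.

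- **Invitation.** A reader might infer that GPs choose whom to invite. The Patients section has invitees selected at random, and GPs only pass on the letter. Labelling at baseline also limits identification bias. The risk lies in who consents and, under the Data collection wording, who visits.
- **Intention to treat.** The statement names no patient set. In a cluster trial it can mean that practices are analysed as randomized, so it is not itself a rival definition of the set. The third version is the abstract's.
- **A combined reading.** The Primary outcome and Data collection sections could be read together as consenters who visited. That reading still makes post-randomization consent a condition, and it leaves the abstract unmatched.
- **Visits.** Counting only attenders is defensible when the outcome is what GPs do at contacts, and no recall of patients is described. Scoring non-attenders as GP non-adherence changes the estimand and is not simply a correction.
- **Exclusions.** Terminal illness and cognitive impairment also appear beside the follow-up approach, but nothing suggests that GP training or chart forms would change them by arm.
- **Condensed article.** Detail on the set may be in the full protocol or the SAP. That excuses omissions, but not statements in the article that conflict with each other.

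**Conclusion.** The point holds as an inconsistency in the primary analysis set. The consenters-only version is formed after randomization, keeps about 30 of 80 labelled patients per practice on the plan's own inputs, can differ by arm and sits badly with the intention-to-treat claim.

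Two stronger readings are tempting and are not supported. One is that the trial will show a false benefit. The illustrative error rates run from 6% to 68% according to assumed selection, and the visit condition could bias the result against the intervention, so neither size nor direction follows from the document. The other is that analysing everyone labelled raises power. That depends on the 40% and 60% rates applying to the full set, and power can fall below the present 81% if non-visitors count as failures.

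**What to change.** Reconcile the abstract, Primary outcome, Data collection and Statistical methods sections around one primary set: patients labelled at baseline in the randomized practices.

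- Take the Table 3 items from records, in pseudonymised form, without making inclusion depend on later patient consent. This is subject to ethics approval, since the document does not show that record review without consent was approved.
- Require individual consent only for questionnaire and interview data.
- State before extraction how patients with no visit are handled, and say what estimand that choice implies.
- Report as sensitivity analyses the consenters-only set and whichever of the visit-based or all-labelled sets is not primary, with consent and visit rates by arm.
- Claim no gain in power.

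The cost is revised wording, an ethics notification and more charts to read: up to 80 per practice instead of about 30. Trial status reports interventions delivered but does not mention follow-up data collection, so on the document's own account the set can still be fixed in advance. If ethics refuses, keep the consent condition, report consent rates by arm and limit the intention-to-treat claim accordingly.
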